| Katz Activities of Daily Living                         | ADL            | 0-6                                            | $< 5$                           | Evaluation of functional independence                                                                                  |
| Mini-Cog                                                | Mini-Cog       | 0-5                                            | $\leq 2$                        | Detection of cognitive impairment in older adults therefore suitable for a more thorough evaluation.                   |
| Flemish version of the Triage Risk Screening Test       | fTRST          | 0-6                                            | $\geq 2$                        | Detection of hospitalized geriatric patients at risk for frailty                                                       |
| Timed Up & Go Test                                      | TUG            | Not applicable                                 | $\geq 20$ sec                   | Three-meters walking test to evaluate functional status                                                                |
| Geriatric 8                                             | G8             | 0-17                                           | $\leq 14$                       | Detection of onco-geriatric patients who may benefit from comprehensive geriatric assessment                           |
| Nutritional Risk Screening                              | NRS            | Normal to severely impaired nutritional status | Moderately to severely impaired | Evaluation of nutritional status taking into account BMI, weight loss and food intake                                  |
| American Society of Anesthesiology score                | ASA            | 1-5                                            | Not applicable                  | Evaluation of preoperative general clinical condition and estimation of anesthesiologic risk                           |
| Charlson Age Comorbidity Index                          | CACI           | 0-42                                           | $\geq 6$                        | Evaluation of cumulative burden of patient's comorbidities                                                             |

Supplementary Table 3. Type of surgical procedures performed

| Procedure                            | Frequency |
|--------------------------------------|-----------|
| Colectomy (left-right-subtotal)      | 434       |

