**MOBILITY**

- I have no problems in walking about ☐
- I have some problems in walking about ☐
- I am confined to bed ☐

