### **3.2 Secondary Objectives**

- To evaluate FR in terms of nutritional status, restoration of daily activities (ADL) and cognitive status (Mini-Cog)
- To evaluate 3 and 6 months postoperative morbidity and mortality
- To obtain prognostic factors for postoperative functional recovery which will assist in the treatment planning /intervention of future elderly patients who are offered surgery for cancer
- To identify variables affecting postoperative quality of life

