# **6 STATISTICAL CONSIDERATIONS**

## **6.1 Data analysis**

The Full Analysis Set (FAS) consists of all registered patients.

The primary endpoint will be measured for all registered subjects who fulfill preoperative and postoperative EQ VAS. Demographic and baseline patient characteristics will be summarized for all patients in the FAS. Continuous-scaled variables (e.g., age) will be summarized with means, medians, standard deviations, quartiles, and minimum and maximum values. Categorical variables (e.g., sex) will be summarized using patient counts and percentages. Study endpoints and variables will be evaluated using descriptive statistics, and the key figures of the distributions will be presented in tables. Univariate analyses will allow for a first overview of potentially influential factors.

Multiple linear regression models will be performed in order to evaluate predictors of functional recovery at 3 months and 6 months after surgery.

Exploratory subgroup analyses will be performed. Missing values will be replaced and estimated using multiple imputations. Furthermore, sensitivity analysis will be executed using complete-case analysis.

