## APPENDIX A: PROTOCOL CHANGES

### REASON FOR CHANGES

The protocol has been amended to include patients with moderate severe cognitive impairment into the primary endpoint evaluation, through the use of the proxy version of the EQ-5D-3L questionnaire. Moreover the procedure for Informed Consent obtainment has been better detailed.

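### Section 6.1 imputes every missing value and makes no exception for a living patient unable to do the Timed Up and Go, so a failed test may be replaced by an imputed time

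*Protocol*

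**What the plan says.** Section 6.1 gives the missing-data rule without exceptions: "Missing values will be replaced and estimated using multiple imputations". It adds that "sensitivity analysis will be executed using complete-case analysis". It names no missing-data assumption and does not distinguish a test the patient could not do from a test missed for another reason.

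TUG and Mini-Cog are scheduled at baseline (section 5.3.1) and at 3 and 6 months (section 5.3.3). Neither list has an entry for inability. Supplementary Table 2 describes the TUG as a "Three-meters walking test to evaluate functional status", gives it no score range, and sets the frailty threshold at 20 seconds or more. Mini-Cog is scored 0-5 with a threshold of 2 or less.

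Patients who cannot walk three metres are within reach of the study. Section 4.3.1 admits palliative as well as curative surgery from age 70, and section 4.3.2 has no functional exclusion. ECOG is recorded up to 4, and the EQ-5D-3L mobility item includes "I am confined to bed".

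On use of the results, section 6.1 says: "Multiple linear regression models will be performed in order to evaluate predictors of functional recovery at 3 months and 6 months after surgery". Section 3.2 defines functional recovery by nutritional status, ADL and Mini-Cog. TUG is not in that definition.

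**The concern.** A patient who attends the visit and cannot do the walk has not left the result unknown: inability is itself the poorest outcome the test can show. Because the TUG is a time in seconds, that outcome has no place on the scale. If it is stored as an empty field, section 6.1 fills it with a finite time.

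Imputation learns mainly from patients who could be tested, so the filled-in values tend to be too good. The planned sensitivity analysis omits the same patients, so it errs in the same direction. Agreement between the two analyses would therefore be false reassurance.

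At stake are the description of mobility and cognition after surgery, and the use of baseline TUG and Mini-Cog as prognostic factors. Placing some of the most impaired patients on the better side of a threshold blurs the contrast that the threshold is meant to show.

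This point concerns living patients who are seen. Deaths and missed visits are a separate matter.

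**Working it through.** **The plan's own figure.** The 265 patients in section 6.2 (paired t-test, effect size 0.2, two-sided 0.05, 90% power) reproduce: the noncentral t distribution gives 265 with power 90.04%, and the normal approximation gives 262.7. That calculation concerns EQ VAS, and nothing below changes it. The plan states no figure for TUG or Mini-Cog.

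**Inputs**
- From the documents: the blanket rule and its check (6.1), the visits (5.3.1, 5.3.3), and the TUG threshold of 20 seconds (Supplementary Table 2).
- Assumed, because the documents give no value: f, the share of living patients seen who are unable to do the TUG, 2-8%; p, the share of tested patients at 20 seconds or more, 10%; q, the share of unable patients whom imputation places at 20 seconds or more, 10% (nothing informative in the model) to 80%.

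**Step 1. Impairment if inability counts as impaired:** T = f + (1 − f)p.
- f = 2%: 0.02 + 0.98 × 0.10 = 11.8%
- f = 5%: 0.05 + 0.95 × 0.10 = 14.5%
- f = 8%: 0.08 + 0.92 × 0.10 = 17.2%

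**Step 2. Complete-case analysis** gives p = 10.0% each time. The understatement is f(1 − p): 1.8, 4.5 and 7.2 points. If p is varied over 5-20%, the range for f of 2-8% becomes 0.02 × 0.80 = 1.6 to 0.08 × 0.95 = 7.6 points.

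**Step 3. Multiple imputation** gives M = (1 − f)p + fq, an understatement of f(1 − q). At f = 5%:
- q = 10%: 0.095 + 0.005 = 10.0%, low by 4.5 points
- q = 20%: 0.095 + 0.010 = 10.5%, low by 4.0 points
- q = 40%: 0.095 + 0.020 = 11.5%, low by 3.0 points
- q = 80%: 0.095 + 0.040 = 13.5%, low by 1.0 point

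At q = 40%, f of 2-8% gives 0.02 × 0.60 = 1.2 to 0.08 × 0.60 = 4.8 points.

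**Step 4. How far do same-visit data help?** A simulation of 200,000 draws used a standardised score (higher is better). The lowest 5% or 10% were untestable and were imputed by linear regression on a covariate with correlation r.

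| r | Imputed mean of untestable, 5% / 10% | Overall mean too good by (SD), 5% / 10% |
|---|---|---|
| 0 | +0.10 / +0.19 | 0.11 / 0.20 |
| 0.5 | −0.35 / −0.17 | 0.09 / 0.16 |
| 0.7 | −0.83 / −0.59 | 0.06 / 0.12 |
| 0.9 | −1.57 / −1.27 | 0.02 / 0.05 |

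The true mean of the untestable group is about −2.07 SD (5%) or −1.75 SD (10%). Good predictors shrink the bias, but at every r tried it remains and has the same sign. The simulation assumes that the untestable are exactly the lowest scorers.

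The effect on TUG and Mini-Cog as predictors was not quantified.

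**The case against.** The strongest reply is that section 6.1 says what is done with missing values, not what counts as missing. A reader might infer that the protocol orders untestable patients to be coded as missing. It does not say so. Section 5.3 refers to a CRF completion manual, which is not shown, and the manual or an analysis plan may assign a code. This stands, and it makes the point conditional. It does not remove it: the rule in 6.1 is stated without exception, and no other category appears in the lists of data to collect. If the reason is not recorded at the visit, a later analysis plan may be unable to recover it.

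A reader might also infer from Appendix A, whose purpose was to "include patients with moderate severe cognitive impairment into the primary endpoint evaluation", that the amendment admitted patients who have no Mini-Cog score. The documents do not support this. The superseded text withheld only the EQ-5D from this group, and it identified the group by a Mini-Cog score below 3, so these patients had a score. Nothing shows that they were ineligible before. Mini-Cog also has a floor of 0. The case therefore rests mainly on TUG, and on Mini-Cog only for the few who cannot attempt it.

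Reach is limited as well. A reader might infer that the main result is biased. The primary endpoint is EQ VAS, and TUG lies outside the definition of functional recovery. Only Mini-Cog touches that outcome directly.

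Nor is the information wholly lost. ADL, ECOG and the EQ-5D are collected at the same visits and can inform the imputation. This stands, and step 4 shows that it reduces the bias.

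Finally, Supplementary Table 2 stands beside tables of results, so its blank TUG range is weak evidence about the prospective plan. The point rests on sections 5.3 and 6.1.

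**Conclusion.** The point holds in a conditional form. Section 6.1 applies one imputation rule to every missing value and makes no exception for inability. If inability is entered as missing, the worst TUG results, and occasionally Mini-Cog results, are replaced by better ones, and the stated sensitivity analysis cannot show it.

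The direction is clear; the size is not given by the documents. With 2-8% unable and 10% impaired among those tested, complete-case analysis understates TUG impairment by 1.8-7.2 points. Imputation understates it by less, depending on how well same-visit data predict inability: at 5% unable, by 3.0 points if 40% of these patients are placed above the threshold and by 1.0 point if 80% are. All these inputs are assumptions.

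The effect falls on secondary descriptive results and on TUG and Mini-Cog as predictors. The primary comparison and the 265 patients are unaffected. The change should be made, but it does not threaten the main conclusion.

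**What to change.** - On CRFs B, 3M and 6M, record for TUG and Mini-Cog 'not done: unable' separately from 'not done: other reason'.
- In section 6.1, count 'unable' as meeting the existing Supplementary Table 2 threshold, for analysis only: TUG 20 seconds or more; Mini-Cog 2 or less, and only where the inability is cognitive.
- Limit multiple imputation to tests not done for other reasons.
- Analyse TUG by its threshold or by rank, so that inability has a place on the scale.

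The cost is one tick-box per test and a short addition to section 6.1. The downside is that TUG is no longer summarised as mean seconds for all patients. Treatment and the sample size do not change.

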## **6.2 Sample size**

A sample size of 265 patients who completed pre and postoperative EQ VAS questionnaires will have a 90% power to detect an effect size of 0,2 between pre and post surgery ,using a paired t-test with a 0,05 two sided significance level.

Given a potential loss to follow-up (about 10%), uncompleted questionnaires (about 10%) and postoperative mortality (about 15%), the sample size will be increased to 350-400 patients (see

ref 18 and 19).

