#### **4.2 Study Design**

GO SAFE is a multicenter international observational prospective cohort study. The study is non-for-profit. Recruiting centers will collect data prospectively. Recruited patients will be followed for 6 months after their surgery. The original treatment plan, as designed by each individual recruiting centre, will not be altered or affected by the study inclusion.

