## **11 PUBLICATION POLICY AND AUTHORSHIP**

Clinical results will be published collaboratively. Interim and final analysis will be presented at scientific conferences to ensure visibility.

Data will be published, acknowledging authorship to all the centers giving a substantial contribution, under the name of "SIOG (International Society of Geriatric Oncology)

surgical task force/ESSO (European Society of Surgical Oncology) GO SAFE study group”.

A maximum of 5 investigators from each individual surgical unit will be included as formal co-investigators in this research, and will be PubMed searchable and citable. The output from this research will be published on behalf of the ”SIOG (International Society of Geriatric Oncology) surgical task force/ESSO (European Society of Surgical Oncology) GO SAFE study group”.

Each hospital may participate with different surgical units (GI, HBP, etc...) and each unit should enrol a minimum number of 20 patients in order to claim authorship.

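### The sample size and the named regression method make no allowance for centre; if EQ VAS change varies between centres, precision and power are overstated

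*Protocol*

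**What the plan says.** All references are to the protocol.

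- **Sample size (6.2).** "A sample size of 265 patients who completed pre and postoperative EQ VAS questionnaires" are said to give "90% power to detect an effect size of 0,2 between pre and post surgery", "using a paired t-test with a 0,05 two sided significance level". Neither an ICC nor a design effect is mentioned. After attrition, "the sample size will be increased to 350-400 patients".
- **Analysis (6.1).** Endpoints are to be described. "Univariate analyses will allow for a first overview of potentially influential factors", and multiple linear regression is named for predictors of functional recovery at 3 and 6 months. No centre term, random effect or robust standard error is named. No test is named for the primary endpoint; the paired t-test appears only in 6.2.
- **Design (4.1, 4.2).** "GO SAFE is a multicenter international observational prospective cohort study". The number of centres is left open, and each centre's own treatment plan is unchanged by the study.
- **Centre data (5.2).** Centre is recorded at registration on CRF A.
- **Unit size (11).** A hospital may join with several surgical units, and "each unit should enrol a minimum number of 20 patients in order to claim authorship".

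**The concern.** Patients treated in one unit share case mix, perioperative practice and access to geriatric care. If the pre-to-post change in EQ VAS differs between units for these reasons, 265 patients carry less information than 265 independent ones. A standard error that ignores this is then too small for the primary mean change.

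The regressions raise a second issue. Several variables collected in 5.3.1 and 5.3.2 are partly properties of the unit: procedure category, surgical approach and geriatric involvement. Section 11 strengthens the link by letting a hospital join with separate units by specialty. For such predictors the standard error can be too small, and the estimated effect can partly be a centre effect. This matters because section 3.2 wants prognostic factors that will guide treatment planning for future patients.

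**Working it through.** **1. Reproduce the protocol's figure.** A paired t-test is a one-sample test on the change. With d = 0.2, two-sided alpha 0.05 and 90% power, the normal approximation is ((1.960 + 1.282)/0.2)² = 262.7, so 263. The exact noncentral t gives 89.93% power at 264 and 90.04% at 265. The stated 265 is therefore the exact answer for independent patients, with nothing added for clustering.

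**2. Inputs that the protocol does not give.**
- ICC of the EQ VAS *change*: assumed 0.01, 0.02 and 0.05.
- Completers per unit, m: illustrative only. Section 11 mentions 20 enrolled. The attrition rates in 6.2 (10%, 10% and 15%) sum to 35%, and 20 × 0.65 = 13. So m = 13 and m = 20 are used, with equal unit sizes.

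**3. Primary mean change.** Design effect DE = 1 + (m − 1) × ICC. The true standard error is √DE times the naive one. Effective n = 265/DE. Power is the noncentral t power at the effective n for d = 0.2, for a test with a correct standard error. The type I error of a test that ignores centre is 2 × [1 − Φ(1.96/√DE)].

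| m | ICC | DE | √DE | Effective n | Power | Type I error if centre ignored |
|---|---|---|---|---|---|---|
| any | 0 | 1.00 | 1.00 | 265 | 90% | 5% |
| 13 | 0.01 | 1.12 | 1.06 | 237 | 87% | 6% |
| 13 | 0.02 | 1.24 | 1.11 | 214 | 83% | 8% |
| 13 | 0.05 | 1.60 | 1.26 | 166 | 73% | 12% |
| 20 | 0.01 | 1.19 | 1.09 | 223 | 84% | 7% |
| 20 | 0.02 | 1.38 | 1.17 | 192 | 79% | 10% |
| 20 | 0.05 | 1.95 | 1.40 | 136 | 64% | 16% |

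**4. Regression slopes.** Here the inflation also depends on how strongly the predictor clusters: variance factor = 1 + (m − 1) × ICC(outcome) × ICC(predictor). With m = 20 and outcome ICC 0.05, this gives the first three columns. The last two are from a simulation of 13 units of 20 patients with 3,000 replicates.

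| Predictor ICC | Variance factor | True/naive SE, formula | True/naive SE, simulated | Type I error, simulated |
|---|---|---|---|---|
| 0 (evenly spread) | 1.00 | 1.00 | 1.00 | 5.3% |
| 0.1 | 1.095 | 1.05 | 1.05 | 6.4% |
| 0.5 | 1.475 | 1.21 | 1.21 | 10.4% |
| 1 (pure centre level) | 1.95 | 1.40 | 1.40 | 16.0% |

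A second simulation at the same outcome ICC gave about 5%, 9% and 17% for predictor ICC 0, 0.5 and 1.

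**The case against.** Four arguments narrow the point.

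- **The handling of centre is often left to the SAP, which is not shown.** This stands in part. Section 6.1 lists no covariates at all and does not exclude centre, so its silence is weak evidence that centre will be ignored. But the sample size is set in the protocol itself, and step 1 shows that it assumes independence.
- **A reader might infer that the cohort consists of units of 20 or more.** Section 11 does not say so. Twenty is a threshold for authorship and counts enrolled patients. Smaller units may contribute, and with 350 to 400 patients at most 17 to 20 units could reach it (350/20 = 17.5; 400/20 = 20). The unit sizes above are therefore illustrations.
- **A reader might infer that every standard error in the study is too small.** That does not follow. The paired difference removes stable centre differences in EQ VAS level, so only between-centre variation in the change matters; with an ICC of 0 nothing changes. Slopes for predictors spread evenly across centres keep a correct standard error (step 4).
- **Power may no longer be the issue.** Supplementary Table 3 totals 942 procedures, well above the 350 to 400 planned. If the analysed cohort is of that size, the power shortfall may not arise. Understated standard errors and confounding by centre would remain, and DE rises with patients per unit.

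**Conclusion.** The point holds in a limited form. The sample size rests on independent patients, and the named regression method does not address centre, in a cohort where centres treat in their own way.

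If EQ VAS change varies between centres with an ICC of 0.01 to 0.05, and units supply 13 to 20 completers, the true standard error of the mean change is 1.06 to 1.40 times the naive one. The 90% power becomes about 87% to 64%, and an unadjusted 5% test runs at about 6% to 16%. Neither the ICC nor the unit size comes from the protocol, so this is a range of scenarios and not an estimate of the bias.

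For the regressions the conclusion applies mainly to predictors that cluster by centre. The documents do not show that the final analysis will ignore centre, only that the protocol neither plans for it nor states the assumption. The change is worthwhile because it is cheap and uses data already collected.

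**What to change.** **Section 6.1.**
- Test the mean EQ VAS change, and fit the functional-recovery regressions, with a random centre (unit) intercept or with cluster-robust standard errors.
- A random intercept alone mixes within-centre and between-centre effects. For predictors that cluster by centre, add centre fixed effects or the centre means of the predictor. A predictor that is constant within a centre cannot be estimated under fixed effects; report it as a between-centre association.
- With few units (265/20 ≈ 13 to 265/13 ≈ 20 in the scenarios above), use a small-sample correction.
- Keep the unadjusted analysis as a sensitivity analysis.

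**Section 6.2.** State that the 90% power assumes no between-centre variation in the change, or restate power over an assumed ICC range such as the table above. This does not require enrolling more patients.

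**Cost.** Model specification and one sentence on power. Centre is already on CRF A; where a hospital contributes several units, confirm that the unit can be identified. The downside is somewhat wider intervals.

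### The lower part of the 350-400 target in section 6.2 does not deliver 90% power under the protocol's own loss rates

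*Protocol*

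**What the plan says.** Section 6.2 sets the evaluable number first: "A sample size of 265 patients who completed pre and postoperative EQ VAS questionnaires will have a 90% power". The target is "an effect size of 0,2 between pre and post surgery", tested "using a paired t-test with a 0,05 two sided significance level". It then lists three expected losses: about 10% lost to follow-up, about 10% with uncompleted questionnaires, and "postoperative mortality (about 15%), the sample size will be increased to 350-400 patients". It does not say how the three rates were combined, and it shows no step from 265 to the range.

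Section 6.1 evaluates the primary endpoint in registered patients who have both a preoperative and a postoperative EQ VAS. Each of the three losses therefore removes patients from the number that section 6.2 is powered on.

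**The concern.** The size, the loss rates and the power are all stated in one section, so they should agree. Inflating 265 for losses of this order gives a number near or above the top of the range, not its bottom. A reader who takes 350 as sufficient would expect 90% power on the primary comparison and would have somewhat less. What is at stake is the accuracy of the stated power. The test, the significance level and the validity of the result are not in question.

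**Working it through.** **Inputs (all from section 6.2).** Effect size 0.2, read as the mean paired difference divided by its standard deviation; paired t-test, two-sided 0.05; power 90%; losses of about 10%, 10% and 15%; target 350-400.

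**Step 1: reproduce 265.** The normal approximation is ((1.960 + 1.282)/0.2)² = 262.7, so 263. Exact power from the noncentral t distribution is 89.93% at n = 264 and 90.04% at n = 265. The protocol's 265 is the exact minimum, with no slack to absorb a shortfall.

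**Step 2: inflate for losses.** Registrations needed = 265 / (1 − total loss).

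- Additive: total loss = 0.10 + 0.10 + 0.15 = 0.35, so 265/0.65 = 407.7, or 408.
- Sequential: retention = 0.90 × 0.90 × 0.85 = 0.6885 (loss 31.15%), so 265/0.6885 = 384.9, or 385.

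**Step 3: what the stated range yields.** Expected pairs = registrations × retention. Power is calculated at the whole number of pairs, rounded down.

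| Registered | Additive: pairs (power) | Sequential: pairs (power) |
|---|---|---|
| 350 | 227 (85.1%) | 240 (87.0%) |
| 375 | 243 (87.4%) | 258 (89.3%) |
| 385 | 250 (88.3%) | 265 (90.0%) |
| 400 | 260 (89.5%) | 275 (91.1%) |
| 408 | 265 (90.0%) | 280 (91.5%) |

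At 350 sequential the unrounded figure is 350 × 0.6885 = 240.975, so the yield is 240 or 241 pairs depending on rounding. The effect detectable with 90% power at 350 is about 0.210 (sequential) to 0.216 (additive), against the planned 0.20.

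**Step 4: how much loss the range tolerates.** To keep 265 pairs, total loss may be at most 1 − 265/350 = 24.3% at 350 registered and 1 − 265/400 = 33.75% at 400. The stated rates combine to 31-35%.

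**A possible origin of the low end.** Multiplying by (1 + loss) instead of dividing by (1 − loss) gives 265 × 1.35 = 358 or 265 × 1.3115 = 348. The protocol does not show its working, so this is only a conjecture.

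**The case against.** **The range contains a valid answer.** Under sequential losses, 385-400 is enough. Under additive losses, 400 is 5 pairs short at 89.5% power: it tolerates 33.75% loss against an assumed 35%, and every input rate is given as approximate. A reader might infer that the whole inflation is wrong or that the whole range fails. The documents do not support that, since it holds only under the additive reading and treats rounded inputs as exact. This objection stands, and it confines the point to the lower part of the range.

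**The losses may overlap.** Patients who die or are lost also return no questionnaire. If uncompleted questionnaires fell wholly within the other two categories, total loss would be 25% (additive) or 23.5% (1 − 0.90 × 0.85), and the need would be 265/0.75 = 353.3, or 354, or 265/0.765 = 346.4, or 347. At 350 with 25% loss, 262 pairs and 89.7% power would remain. That would nearly rescue 350. However, section 6.2 lists three separate causes and states no overlap. What stands is that the combination rule needs to be written down.

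**Multiple imputation.** Section 6.1 plans it for missing values, with complete-case analysis as the sensitivity analysis. It does not rescue the low end, because the same section limits the primary endpoint to patients with both EQ VAS values and section 6.2 is powered on completers.

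**No rule stops the study at 350.** Sections 4.1, 4.3 and 6.3 describe open participation of centres, consecutive enrolment and a 24-month recruitment period. Supplementary Table 3 totals 942 procedures, and in Supplementary Table 4 the 494 patients with a complication are 52.4%, which implies about 943 patients. This stands and lowers the severity.

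**Conclusion.** The point holds for the lower part of the range. At 350 registered, the protocol's own loss rates leave about 227-241 pairs and power of about 85-87%, at worst about 5 points below the stated 90%. The shortfall shrinks as registrations rise. It disappears at 385 if losses are sequential and at 408 if they are additive, and at 400 the target is essentially met on either reading.

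This rests on taking the three rates at face value as separate losses and on the effect size of 0.2 as section 6.2 uses it.

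A reader might also infer that the study was underpowered. The documents do not support that. Taking 942 as the number registered, a 35% loss would leave 942 × 0.65 = 612 pairs, more than twice the 265 required. The realised number of completed pairs is not given, so this indicates that achieved power was not affected but does not measure it. The severity is minor to moderate: a stated pairing of size and power needs correcting, with no effect on the analysis.

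**What to change.** In section 6.2, state how the three losses combine and whether any of them overlap. Then make one of two changes:

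- replace the range with a minimum of 385 registered patients (sequential, 265/0.6885) or 408 (additive, 265/0.65); or
- keep 350-400 and give the power as about 85-91% over that range, depending on how the losses combine.

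The cost is a sentence or two of text. No analysis changes, and with 942 procedures recorded no extra recruitment is needed. If the second option is chosen, the stated power becomes slightly less favourable at the low end.
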